### Sample and recruitment

The trial started the recruitment in September 2014 and it is still active. The study is conducted in five different Public Mental Health Centers and Primary Care Centers in Spain, namely, the Elda Clinical General Hospital, the Hospital Clínico Universitario de Valencia, the [name] Hospital, the PCC IIA Milagrosa of Pamplona, and the Hospital Comarcal de Vinaròs. Participants are individuals over 18 years of age seeking psychological assistance in the Spanish Public Health System. Sample size was set to 220 participants to ensure enough statistical power when testing our hypotheses (see “Sample size” section).

Patients are referred to the study by licensed psychologists, psychiatrists, and clinical psychology residents working at the collaborating centers, who also assess for current DSM diagnoses (See “measures” section) and the remaining eligibility criteria (see “Inclusion and exclusion criteria” section). Individuals with comorbid diagnosis of several EDs are also enrolled in the study. The existence of such comorbidities might be important for assessment scores. However, in the present study we did not stratify considering comorbidities because this could significantly increase the complexity of the design (i.e., some patients might have more than one comorbid diagnosis). Due to the difficulties derived from conducting an RCT in different public mental health settings, we cannot guarantee a 100% of independent evaluations. We expect between 60 to 75% of independent evaluations. The rest of evaluations will probably be made by recruiters who are also the therapists in one of the conditions. However, this information is collected and considered in the interpretation of results.

Patients meeting eligibility criteria are asked to participate and are provided with an information sheet, information on data confidentiality, and an informed consent form. After participation acceptance, patients complete the baseline assessment protocol in their correspondent health center (see “Measures” section). Next, participants are informed of the condition they have been randomly assigned to, that is, TAU or UP.

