### Sample size

To calculate the sample size required, the non-inferiority margin (i.e., tolerable amount of effect difference between TAU and the UP) has to be set. This was done according to the US Food and Drug Administration (FAD) [16] guidelines. First, the effect of the active control (i.e., CBT) compared with placebo needs to be established, based on previous research. Meta-analyses indicate medium-to-large effect sizes (between .4 and .8) of individual CBT on EDs [17–19]. Then, an amount of minimum preserved effect needs to be set. According to FDA guidelines, a preserved effect of a 50% of the effect of the active control (individual CBT) is recommended, so this was set to .3 in the present study. Because, to the best of our knowledge, no meta-analysis has reported effect sizes for each outcome included in the study, the margin has been defined according to the pooled estimate of overall effectiveness of CBT.

With regards to treatment satisfaction, a 35% non-inferiority margin was established. This is based on a meta-analysis of computer CBT, in which between 70% and 100% of depressed patients were satisfied with treatment [20]. To the best of our knowledge, there is no meta-analysis of treatment satisfaction with individual, face-to-face CBT and its study is rare. However, similar to group UP, computer CBT has been argued to be an alternative to traditional CBT [20], especially when resources are limited, so the aforementioned satisfaction rates of computer CBT might be relevant in the present study.

We obtained a sample size of 95 participants for each group with 80% power, an alpha level of .05 (one-sided), a standard deviation of .83 in the CBT group compared with placebo, and a non-inferiority limit of .30 [21, 22]. Considering a drop-out of 15%, we decided to recruit 110 subjects in each group. When registering the study, a sample size of 200 individuals was calculated. However, this was increased by 20 patients after considering non-inferiority sample size calculations.

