### Procedure

Randomization has been performed by a researcher unrelated to the study using a computer-generated sequence (Randomizer). In the program, the researcher generated 1 set of numbers with 220 numbers, which had a 1-to-2 range. Randomization is stratified according to the severity of the primary measures of depression (BDI-II) [23, 24] and anxiety (BAI) [25, 26], using the recommended cut-off in manuals. In the BDI-II, these are 0–13 for normal, 14–19 for mild, 20–28 for moderate, and for 29–63: severe depressive symptoms [24]. As for anxiety symptoms (BAI), cut-off are 0–7 for normal, 10–18 for mild, 16–25 for moderate, and 26–63 for severe [26]. Stratification is made to ensure a comparable proportion of severely depressed and anxious individuals in each group. For each subgroup (i.e., severe or less severe depression and/or anxiety), participants are randomly assigned to the UP or to TAU. In the UP condition, there are between 8 and 10 participants and 2 clinicians (therapist and co-therapist) per group. In the TAU condition, participants receive individual sessions with one therapist.

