### Analyses

First, we will calculate between-group differences in baseline measures, to ensure that randomization resulted in comparable groups. When normally distributed, continuous data will be analyzed via *t* test. If the Kolmogorov-Smirnov test indicates a non-normal distribution, a Mann-Whitney *U* test will be preferred. A chi-square test will be performed for categorical data. Then, to compare the efficacy of treatments, we will use a mixed-effects regression modeling with full information maximum likely hood estimation. This method is recommended over repeated-measures ANOVAs due to its flexibility in handling missing data [39]. Group (TAU or UP) will be used as the between-subject factor and time (baseline, post-treatment, and follow-ups) as the within-subject factor. Standardized effect sizes (Cohen’s *d*) will be calculated both for within and between-group analyses. Covariates will be demographic and clinical variables that are not comparable between groups, as exposed in the beginning of this section. Effect estimators in the UP group will be adjusted to control for the impact of group dependencies (i.e., homogenization of response to treatment due to shared environment), following the recommendations of Baldwin et al. [40].

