Our study has also some limitations. First, some people who ask for treatment in the public mental health system prefer individual treatment, which could be a barrier when randomly assigned to a group format (i.e., dropout or decreased satisfaction and efficacy of the UP). To control for this, we will explore the effect of format preference and format assignment on treatment adherence and effectiveness. Additionally, as conditions differ in terms of type of therapy (CBT vs. UP) and format (individual vs. group), it will be difficult to ascertain what was responsible for the results. Despite the present study only seeks to find whether the UP in a group format can be an alternative to the traditional psychological treatment in public settings in Spain (i.e., individual CBT), results should be interpreted with caution and no conclusions can be drawn on whether results are due to differences in the type of therapy, its format, or both. In line with the previous, it is important to note that the usual treatment was not stabilized across clinicians at centers (i.e., duration of sessions and treatment) precisely to ensure that the newly tested treatment, namely the UP in a group format, was compared against the usual treatment in Public Mental Health Settings in Spain. It is also important to note that, due the multicenter nature of the study, interventions are conducted by different clinicians, so implementation could differ across centers. In order to minimize this effect, a certified UP Researcher/Trainer, [name], has been in charge of the full treatment for the first two groups at all collaborating centers. All clinicians will act as co-therapists of one group at their working center. Also, when they start treatment they will receive a videoconference supervision before every session by [name] Despite this is done to promote fidelity to the protocol, it is important to note that assessment of fidelity is not performed by an independent rater, so true fidelity cannot be ensured. Finally, another shortcoming is that interviewers using the ADIS are not blind to treatment arm. This was not possible due to legal reasons (data collection at participating hospitals had to be done by a psychologist/psychiatrist working at the center). Due to time restrictions of psychiatrists, this was done by psychologists, who were also in charge of treatment. Despite this limitation, it is important to note that the ADIS is an objective, structured interview, and that on each assessment two interviews are independently made by two different psychologists, which should reduce the likelihood of biases.

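### The only clustering adjustment named is for UP therapy groups; TAU therapists are not modelled, so the one-sided bound is too narrow if therapists differ and are not shared equally between arms

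*Protocol article*

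**What the plan says.** The Analyses section of the protocol article compares the arms with a mixed-effects regression fitted by full information maximum likelihood, with treatment group and time as factors. On dependence between patients it states one rule: "Effect estimators in the UP group will be adjusted to control for the impact of group dependencies". The reason given is shared environment within a therapy group. The random effects of the model are not listed.

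On how TAU is delivered, the Procedure section says: "In the TAU condition, participants receive individual sessions with one therapist". The Discussion says that "the usual treatment was not stabilized across clinicians at centers (i.e., duration of sessions and treatment") and accepts that implementation could differ across centres; the remedies it describes are training and supervision for UP. The TAU section lets clinician and patient agree when treatment ends and makes number of sessions a covariate. No section mentions a therapist or centre term.

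On whether therapists are separate by arm there is only a hint, in a sentence of Sample and recruitment about who carries out the non-independent evaluations: "The rest of evaluations will probably be made by recruiters who are also the therapists in one of the conditions".

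**The concern.** Patients are randomised individually, but treatment can make outcomes dependent in both arms: UP patients share a group, and TAU patients share a therapist with the rest of that therapist's caseload. The stated rule covers the first source only. If it is applied as written, the TAU mean enters the UP–TAU contrast with the variance of independent patients.

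Non-inferiority is declared when an upper one-sided confidence bound lies below the margin. Leaving out a positive variance component pulls that bound towards the estimate, which favours declaring non-inferiority. BDI-II and BAI are both analysed this way.

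**Working it through.** **Inputs from the Sample size section.** The result stated there is: "We obtained a sample size of 95 participants for each group with 80% power". Its inputs are a one-sided 5% test, an SD of .83 and a margin of .30. The Procedure section gives UP groups of 8 to 10; I use 9.

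**Reproducing the plan's figure.** n per arm = 2 × .83² × (1.645 + .842)² / .30² = 94.6, so 95. The stated figure is reproduced as a calculation for independent patients, with no clustering allowance in either arm.

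**Assumptions, because the article gives no figures.** J TAU therapists with equal caseloads of 95/J, who treat TAU patients only; J from 5 to 20; ICC .02, .05 or .10, the same for UP groups and TAU therapists; UP clustering handled correctly.

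**Formulas.**
- Design effects: DE_UP = 1 + (9 − 1) × ICC; DE_TAU = 1 + (95/J − 1) × ICC.
- SE with TAU clustering ignored: SE_model = .83 × √[(DE_UP + 1)/95].
- True SE: SE_true = .83 × √[(DE_UP + DE_TAU)/95].
- True one-sided error at the margin: Φ(−1.645 × SE_model/SE_true).
- Power shown by the test that ignores TAU clustering: Φ[(.30 − 1.645 × SE_model)/SE_true].
- Power of the test that models it: Φ(.30/SE_true − 1.645).

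**One case in full (ICC .05, J = 5).** DE_UP = 1.40 and DE_TAU = 1 + 18 × .05 = 1.90. SE_model = .83 × √(2.40/95) = .132 and SE_true = .83 × √(3.30/95) = .155. The distance from estimate to bound is .217 when TAU clustering is ignored and .254 when it is included. True error = Φ(−1.645 × .853) = 8.0%. Power is 70.4% ignoring TAU clustering and 61.6% modelling it, a gap of 8.8 points.

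**Range (true one-sided error; power gap in points).**

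| TAU therapists | ICC .02 | ICC .05 | ICC .10 |
|---|---|---|---|
| 5 | 6.4%; 4.0 | 8.0%; 8.8 | 10.0%; 14.1 |
| 8 | 5.9%; 2.4 | 6.9%; 5.7 | 8.1%; 9.6 |
| 10 | 5.7%; 1.9 | 6.5%; 4.5 | 7.5%; 7.8 |
| 15 | 5.4%; 1.2 | 5.9%; 2.9 | 6.6%; 5.1 |
| 20 | 5.3%; 0.9 | 5.7%; 2.1 | 6.1%; 3.7 |

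Simulated trials with maximum likelihood fits (11 UP groups of 9) gave similar or somewhat higher error: 8.7% for 5 therapists and 6.8% for 8 at ICC .05, and 11.2% and 9.6% at ICC .10.

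**The opposite case.** If the same therapists treat equally in both arms, their effects cancel in the contrast. A simulation with 5, 10 or 20 such therapists, ICC .02 to .10 and no extra UP group effect gave error of 4.3% to 4.9%, so no inflation. With a TAU therapist ICC of zero there is none either.

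**The case against.** The strongest reply is that much of this rests on silence. The article is condensed, lists no random effects at all, and never says that TAU patients are treated as independent; the full plan may hold a therapist term. That stands as a limit on the wording: a reader might infer that the plan declares TAU patients independent, and the text does not support that. It does not remove the point. The article raised clustering and confined the remedy to one arm and one source, so following it as written leaves TAU therapists out.

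Second, separation of therapists by arm is not documented. The sentence on recruiters concerns evaluations, the therapist section describes one pool, and the Discussion has all clinicians acting as co-therapists of a UP group at their centre. Partial overlap is therefore possible and would shrink the inflation. Equal sharing fits poorly, however, with the Discussion's statement that a certified UP trainer took full charge of the first two groups at all centres. If that means two at each of five centres, it is 10 of about 12 UP groups (110/9 ≈ 12).

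Third, the number-of-sessions covariate may absorb the part of therapist variation that works through treatment length. This is fair: the remaining ICC could be smaller. It is not a therapist term, though.

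Fourth, TAU therapists may be numerous, since recruitment runs over several years at five centres. With 20 of them the inflation is at most about 1.1 points in the table.

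Unstandardised care makes therapist differences plausible but does not measure them. The experience range of 2 to 20 years covers all study therapists, so it cannot show that variation is larger in TAU.

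**Conclusion.** The concern holds conditionally. The only stated clustering adjustment is for UP groups, and no section models TAU therapists. If TAU therapist variance is positive, is left out, and therapists are not equally shared between arms, the bound is too narrow in the direction that favours non-inferiority.

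The consequence ranges from negligible (many therapists, low ICC) to a doubling of the nominal error (five therapists, ICC .10). The ICC, the caseloads and the separation of therapists by arm are my assumptions.

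A reader might go further and conclude that the bound is certainly too narrow, or that the ADIS diagnosis is affected to the same degree. The document does not establish the first, and the calculations here cover a continuous outcome only. The point deserves a change because the remedy is cheap and the rule concerned decides the trial's conclusion.

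**What to change.** Replace the UP-only adjustment with wording such as: *The mixed model will include a random therapy-group intercept in the UP arm and a random therapist intercept for the TAU arm, with arm-specific residual variances. Where a therapist works in both arms, therapist identity will be coded across both. The UP–TAU contrast and its one-sided bound will use REML with Satterthwaite or Kenward-Roger degrees of freedom.* Coding by identity matters because a TAU-only intercept would be misspecified for therapists who work in both arms.

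Record a therapist code on the sheet that TAU clinicians already complete, record the therapists of each UP group in the same way, and report both ICCs.

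**Cost.** No extra patients or visits. The bound widens, and power falls below what the unadjusted test shows: by about 2 to 9 points at ICC .05, and by up to about 14 at ICC .10 with five therapists. With very few TAU therapists the small-sample correction can be conservative (simulated error 3.5–4.9%). If the ICC is near zero, little is lost.

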So far, studies exploring the effectiveness of the UP in a group format have led to promising findings [12–15].Overall, results suggest that the UP obtains medium-to-large effect sizes on numerous outcomes, including depression, anxiety, positive and negative affect, quality of life, overall adjustment, and avoidance of negative sensations, for both anxiety and mood disorders [12–14]. These studies have also revealed that between half and two thirds of patients ceased to meet diagnostic criteria after the treatment and one investigation, conducted by our team, revealed that changes remained stable 12 months after treatment completion [13]. Despite the previous results are encouraging, conclusions should be interpreted with caution as sample sizes have been small (11 participants in two studies and 47 patients in one investigation). Methodologically-sound, randomized, controlled trials are needed in order to replicate the aforementioned findings and to elucidate whether the UP in group format is indeed an effective treatment option for EDs in public settings.

The present non-inferiority, randomized, controlled trial will compare the efficacy of the UP in group format against traditional individual CBT treatment in a sample of patients with EDs. Ultimately, our goal is to explore whether the UP in group format can be an effective psychological intervention for EDs in the Spanish National Health System, that is, one that generates long-lasting changes in symptoms. To ensure the generalizability of results, our goal is tested in various public mental health centers in Spain.

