To address problems of missing data or premature dropouts, an intention-to-treat analysis will be used and the most recent data will be imputed (last observation carried forward approach). This analytic strategy will only be performed with patients attending at least 50% of sessions, as recommended in past research [41], and with those responding to at least one of the post-treatment assessments (i.e., end of treatment or follow-ups) so that treatment effect may be captured by the last observation. In addition to the last observation forward, missing data in the UP group will also be replaced with the CBT mean +/− the non-inferiority margin and missing data in the CBT group will be replaced with the UP mean (i.e., bias toward inferiority) [42]. Results using a last observation carried forward approach and a bias toward inferiority imputation will be compared against a completers-only strategy and all of them will be reported. To ensure non-inferiority, a per-protocol analysis will also be conducted. Following FDA guidelines [16], non-inferiority will be concluded if the upper bound of the 95% CI for the effect estimate in the UP condition is smaller than the non-inferiority margin (50% of the effect estimate of individual CBT when compared to placebo). Due to the non-inferiority design (i.e., the Unified Protocol in a group format is not worse than individual CBT), a one-sided confidence interval will be used in the analyses. A post-hoc power analysis with the primary outcomes will be conducted at post-treatment and follow-ups using the sample size and obtained effect size.

The researcher analyzing data, [name], will be blind to arm allocation. To ensure that, arms will be given arbitrary letters (A and B) in the database and only the lead researcher, [name], will know the correspondence between study allocation arms and assigned arbitrary letters.

Reporting of results will follow the Consolidated Standards of Reporting Trials (CONSORT) recommendations [43].

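### Last observation carried forward (LOCF) assumes no further relapse in patients lost during follow-up, attenuates a late difference in proportion to missing visits, and overlays a mixed model that does not need it

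*Protocol article*

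**What the plan says.** All references are to the protocol article.

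- **Missing data (Analyses).** For missing data and premature dropouts, "an intention-to-treat analysis will be used and the most recent data will be imputed (last observation carried forward approach".
- **Who enters that analysis (Analyses).** There is an attendance condition: "This analytic strategy will only be performed with patients attending at least 50% of sessions". There is also a data condition: "with those responding to at least one of the post-treatment assessments (i.e., end of treatment or follow-ups) so that treatment effect may be captured". The carried value is therefore always a score from end of treatment or later, never baseline.
- **Companion analyses (Analyses).** A bias-toward-inferiority imputation is added, in which "missing data in the UP group will also be replaced with the CBT mean +/− the non-inferiority margin" and missing CBT values take the UP mean. LOCF and bias-toward-inferiority results "will be compared against a completers-only strategy and all of them will be reported". A per-protocol analysis follows. The section does not say which result decides non-inferiority.
- **Efficacy model (Analyses).** Treatments are compared by mixed-effects regression with full information maximum likelihood over baseline, post-treatment and follow-ups. The stated reason is: "This method is recommended over repeated-measures ANOVAs due to its flexibility in handling missing data".
- **Aim (Background).** The goal is an effective intervention, "that is, one that generates long-lasting changes in symptoms". Methods/design sets follow-ups at 3, 6 and 12 months after treatment.

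**The concern.** The follow-up visits exist to show whether gains last. For a patient who stops attending, LOCF answers that question by assumption: the last score seen becomes the score at every later visit. A patient seen only at end of treatment supplies the 3-, 6- and 12-month results from that single value.

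In a superiority trial, shrinking a difference is often conservative. In a non-inferiority trial it is the reverse when the new treatment is the one that deteriorates, because the shrinkage moves the estimate away from the margin. The comparison here is between a fixed 12-session group programme and individual treatment of open duration. Whether one arm relapses more after treatment is a real question, and the documents do not settle it.

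The imputation also sits awkwardly with the model named in the same section. A likelihood-based mixed model uses each patient's observed visits. Once LOCF has filled the later visits, those visits are no longer missing for the model to handle.

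**Working it through.** **Inputs (Sample size section).** Non-inferiority limit .30; SD .83; one-sided alpha .05; power 80%; 95 per arm, raised to 110 for 15% drop-out.

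**The plan's own figure.** n per arm = 2(1.645 + 0.842)² × .83² / .30² = 94.7, rounded up to 95. This matches. For drop-out, 95 × 1.15 = 109.3 (110) and 95 / .85 = 111.8 (112). The stated 110 is the first of these and close to the second.

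**Scenario.** Higher scores are worse. The arms are equal at end of treatment, and UP is truly worse by exactly .30 at 12 months. A share m of each arm, lost at random, has its end-of-treatment score carried forward. The 15% is the plan's drop-out figure; applying it to follow-up loss is an assumption, as is the 30%.

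**Expected difference under LOCF** = (1 − m) × .30.
- m = 15%: .85 × .30 = .255
- m = 30%: .70 × .30 = .21

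**False non-inferiority** = Φ([.30 − (1 − m) × .30] / SE − 1.645), with SE = .83 × √(2/n).

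| Share carried | n = 95, SE .1204 | n = 110, SE .1119 |
|---|---|---|
| 0% | 5.0% | 5.0% |
| 15% | Φ(.045/.1204 − 1.645) = 10.2% | Φ(.045/.1119 − 1.645) = 10.7% |
| 30% | Φ(.09/.1204 − 1.645) = 18.5% | Φ(.09/.1119 − 1.645) = 20.0% |

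Allowing for the slightly larger variance of a mixture of carried and observed scores lowers these rates by less than 0.2 percentage points. A simulation of 10,000 trials with 110 per arm and an assumed within-patient correlation of .6 gave 10.4% at 15% and 20.0% at 30%. In a separate simulation of the same scenario, observed values only gave 5.0% and 5.2%.

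**Unequal loss with equal relapse.** If both arms relapse by r, the LOCF bias in UP minus TAU is −(m_UP − m_TAU) × r. With assumed losses of 25% and 10%, it is −.15 × .3 = −.045 for r = .3 and −.15 × .5 = −.075 for r = .5. Both favour UP, against a margin of .30.

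**Does bias toward inferiority repair it?** Take the unfavourable sign, with the CBT mean at 0 and the UP mean at .30. The UP arm becomes (1 − m) × .30 + m × (0 + .30) = .30. The CBT arm becomes (1 − m) × 0 + m × .30 = .30m. The difference is .30(1 − m), the same as under LOCF. Simulated false non-inferiority was 7.2% at 15% and 12.4% at 30%: closer to 5%, but not restored.

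**The case against.** The strongest reply is that LOCF is one of several planned analyses. The plan also contains a mixed model suited to incomplete data, a deliberately unfavourable imputation, a completers-only comparison and a per-protocol analysis, and it undertakes to report the results side by side. In the scenario above, completers-only would show the full .30 at the 5% error rate, so a reader would see the discrepancy. This stands as mitigation. It is not a cure: no analysis is named as decisive, completers-only is itself biased if relapse drives loss, and bias toward inferiority does not restore the difference here.

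Four stronger readings are tempting, and the documents do not support them.

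- *LOCF hides any difference in relapse.* It acts only on missing visits. Observed scores still show relapse, and at 15% carried, .255 of .30 remains visible.
- *Relapse is set to zero for every lost patient.* A patient last seen at 3 or 6 months carries that score, including any relapse up to then. The calculation takes the extreme case in which every carried score dates from end of treatment.
- *The bias always favours UP.* It does so only if UP relapses more, or if both arms relapse and UP loses more patients. The Discussion recognises that assignment to groups against preference may cause dropout, so the second is plausible. But Background reports stable gains at 12 months in an earlier group UP study, and if TAU relapsed more, LOCF would understate an advantage of UP.
- *The 12-month error rate is the trial's error rate.* The plan does not make 12 months the deciding time.

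It is also fair to say that 95 per arm is already net of drop-out, so applying a further loss to it counts loss twice. The 110-per-arm column avoids this and gives slightly higher rates.

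**Conclusion.** The point holds as one of attenuation. Under the intention-to-treat label, the plan uses an imputation that assumes no further change in lost patients, in a trial that names durability as a goal, and lays it over a model that needs no single imputation.

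If UP is truly worse by the margin at 12 months, 15% carried forward shows .30 as .255 and raises one-sided false non-inferiority from 5% to about 10 to 11%. At an assumed 30% it is about 18 to 20%. These figures rest on equal arms at end of treatment, loss at random and equal in both arms, every carried score dating from end of treatment, and a true difference exactly at the margin. The protocol gives only an overall drop-out figure and no loss rate by follow-up visit. With TAU relapsing more, the direction reverses.

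The practical risk is that, with several results reported and none decisive, a favourable LOCF result could carry the conclusion.

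**What to change.** 1. State that no value is carried forward into the 3-, 6- or 12-month visits.
2. Name the mixed model already in the Analyses section, fitted to the observed visits of all randomised patients, as the deciding analysis for follow-up non-inferiority and for any statement that gains were maintained.
3. Report the numbers observed per visit and arm.
4. Keep bias toward inferiority as a sensitivity analysis and replace the open +/− with the sign unfavourable to UP. Read it alongside the main result rather than as a guarantee, given the calculation above.

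The cost is analysis wording only; no visit, measure or patient is added. Follow-up intervals will be wider than LOCF would show. With 15% missing and no information recovered from earlier visits, the factor is √(1/.85) = 1.085, or about 8% wider. The mixed model should recover part of that.
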